## **3.8 Data management and analysis**

### **3.8.1 Data management**

The research report form is filled in by the research object and the result evaluation personnel. The research report form consists of an activity log sheet, a blood lipid measurement sheet, a body composition measurement sheet, a physical fitness measurement sheet, and an adverse event record sheet. After the completed research report sheet is reviewed by the project manager, the data entry clerk is organized to enter the data and Unified management of the original table.

### **3.8.2 Data analysis**

Data will be collected by means of Excel 2019, statistical analysis will be carried

out using the IBM SPSS version 26.0 (IBM Corporation, NY, USA). Data will be present as mean  $\pm$  standard deviation (SD), and 95% confidence interval (CI) adopted. A normality study will be conducted and further descriptive statistics will be carried out. The Shapiro-Wilk test will be used to test whether the data conform to a normal distribution. If the parameters are normally distribution, the one-way ANOVA test will be used to compare the three groups, the independent t-test will be used for two groups comparison, and the Paired t-test will be used to compare the results before and after training within the group. If the parameter is Non-normally distribution, the Kruskal Wallis test will be used to compare the three groups, the Mann-Whitney u test will be used for two groups comparison, and the Wilcoxon rank test will be used to compare the results before and after training within the group. The level of statistical significance will be set at  $p < 0.05$ .

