## **2. Objectives of the study**

Using randomized controlled trials, one is to evaluate the effects of two different Tai Chi exercises on the physical fitness and blood lipids of overweight male college students, and the other is to compare the effects of two different Tai Chi on physical fitness and blood lipids.

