### 3.3 Sample size

The purpose of this study is to evaluate the effect of the newly compiled Bafa Wubu simplification Tai Chi and traditional He-style Tai Chi on the blood lipids and physical fitness of overweight college students. Therefore, using a randomized controlled trial study design (RCT). Since blood lipids are the main outcome variable of the study, however, the previous research literature did not have 3 groups of test subjects similar to this research, similar exercise intensity and similar parameters. Therefore, G Power 3.1.9.4 is used to estimate the sample size. Since the experiment is designed into three groups, select "ANOVA: Fixed effects, omnibus, one-way" in F tests, select "A priori: Compute required sample size" in Analysis, and set the effect size conventions to the maximum value  $f=0.40$ ,  $\alpha$  err prob is set to 0.05, power ( $1-\beta$  err prob) value is set to 0.80, Number of groups is set to 3. The calculation steps are as follows:

The screenshot shows the G\*Power 3.1.9.4 software window. The 'F tests' tab is selected, and the 'ANOVA: Fixed effects, omnibus, one-way' test is chosen. The 'Analysis' section is set to 'A priori: Compute required sample size'. The 'Input' parameters are: Effect size  $f = 0.40$ ,  $\alpha$  err prob = 0.05, Power ( $1-\beta$  err prob) = 0.80, and Number of groups = 3. The 'Output' parameters are: Noncentrality parameter  $\lambda = 10.5600000$ , Critical F = 3.1428085, Numerator df = 2, Denominator df = 63, Total sample size = 66, and Actual power = 0.8180744. The 'Test family' is 'F tests' and the 'Type of power analysis' is 'A priori: Compute required sample size - given  $\alpha$ , power, and effect size'. The 'Input Parameters' section shows 'Determine =>' with 'Effect size f' set to 0.40, ' $\alpha$  err prob' set to 0.05, 'Power ( $1-\beta$  err prob)' set to 0.80, and 'Number of groups' set to 3. The 'Output Parameters' section shows 'Noncentrality parameter  $\lambda$ ' set to 10.5600000, 'Critical F' set to 3.1428085, 'Numerator df' set to 2, 'Denominator df' set to 63, 'Total sample size' set to 66, and 'Actual power' set to 0.8180744. A 'Calculate' button is visible at the bottom right.

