### **3.6 Data collection**

Visit 1 (Baseline): Before the test, all participants performed basic personal physical sign evaluation and filled out the personal physical sign evaluation form. The evaluation content included gender, age, body height, body weight, and BMI value.

Visit 2 (Pre-training): All participants will participate in blood lipid assessment (TC, TG, LDL-C, HDL-C), physical fitness assessment (Body mass, BMI, fat percentage, muscle content, flexibility, upper and lower limbs Strength, balance and aerobic endurance).

Visit 3 (Post-training): All participants will be participated in the examination as same as the assessment of visit 2.

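### Section 3.8.2 compares the groups without baseline adjustment, leaves the analysed variable unstated, and uses the pre-training value explicitly only in uncontrolled within-group tests; ANCOVA on the Visit 2 value would gain precision at no cost

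*Protocol*

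**What the plan says.** Section 2 gives two objectives. The first is stated as "one is to evaluate the effects of two different Tai Chi exercises on the physical fitness and blood lipids of overweight male college students"; the second is to compare the two Tai Chi types with each other.

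Section 3.6 provides a baseline for every outcome. At Visit 2, "All participants will participate in blood lipid assessment (TC, TG, LDL-C, HDL-C), physical fitness assessment" takes place, and the list there covers body composition, flexibility, strength, balance and endurance. At Visit 3, "All participants will be participated in the examination as same as the assessment of visit 2".

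Section 3.8.2 names the tests. For data that pass Shapiro-Wilk, the rule between groups is that "the one-way ANOVA test will be used to compare the three groups, the independent t-test will be used for two groups comparison". Inside each arm a different rule applies, with no reference to the control group: "the Paired t-test will be used to compare the results before and after training within the group". For data that fail, Kruskal-Wallis and Mann-Whitney take over between groups. Inside each arm the replacement is again a before-after test: "the Wilcoxon rank test will be used to compare the results before and after training within the group". One significance level, p<0.05, covers all of these. No covariate, change score or group-by-time term is mentioned, and no test is tied to either objective.

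**The concern.** The first objective needs Tai Chi minus control, and the second needs one Tai Chi type minus the other. Both are between-group contrasts. As written, those contrasts have no baseline term, so on a post-only reading they carry all the stable variation between men in weight, fat and lipids. Adjustment for the Visit 2 value would remove much of it.

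The one place where before and after are explicitly compared is inside each arm, without a control. A change there may come from Tai Chi, from term-time routine or season, or from repeating the same fitness tests. The control arm exists to separate these, and the paired tests do not use it. Because section 3.8.2 does not say which test answers the first objective, a significant paired test in a Tai Chi arm could be taken as the answer. A contrast of the form 'significant in Tai Chi, not significant in control' is not a test of a difference between the arms.

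**Working it through.** **Inputs from the Protocol.** Section 3.3: f = 0.40, alpha 0.05, three groups, N = 66, power 0.8180744, critical F 3.1428085; 30 per group planned (N = 90). Section 3.1.1: 1:1:1 allocation.

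**Assumptions, not in the Protocol.** Pre-post correlation rho (0.3 to 0.7 shown), equal variance at both visits, a smaller effect f = 0.25, and a drift common to all arms of 0 to 0.5 SD.

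**Step 1: the plan's own figure.** Noncentral F with lambda = f²N = 0.16 × 66 = 10.56 and df 2 and 63 gives critical F 3.14281 and power 0.81807, an exact match. N = 63 gives 0.798, so 66 is the smallest balanced total that reaches 80%. N = 90 gives 0.926.

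**Step 2: variance relative to a post-only comparison.** ANCOVA: 1 − rho². Change score: 2(1 − rho).

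| rho | ANCOVA | Change score |
|---|---|---|
| 0.3 | 0.91 | 1.40 |
| 0.5 | 0.75 | 1.00 |
| 0.7 | 0.51 | 0.60 |

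**Step 3: omnibus power at f = 0.40, N = 66.** For ANCOVA, f becomes f/√(1 − rho²) with df 2 and 62. For change scores it becomes f/√(2(1 − rho)) with df 2 and 63. At rho = 0.7 these are 0.40/√0.51 = 0.560 and 0.40/√0.60 = 0.516.

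| rho | Post-only | Change score | ANCOVA |
|---|---|---|---|
| 0.3 | 0.818 | 0.668 | 0.854 |
| 0.5 | 0.818 | 0.818 | 0.917 |
| 0.7 | 0.818 | 0.965 | 0.984 |

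The total N for 80% power under ANCOVA falls from 66 to 60, 51 and 36 respectively. Even at rho = 0, ANCOVA power at N = 66 is still 0.818, so the lost degree of freedom costs practically nothing.

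**Step 4: a smaller effect.** At an assumed f = 0.25 and N = 90, post-only power is 0.540. ANCOVA gives 0.671 at rho = 0.5 and 0.840 at rho = 0.7.

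**Step 5: the paired tests when Tai Chi has no effect.** Let every arm drift by d SD. The standardised change is d/√(2(1 − rho)). With d = 0.3 and rho = 0.7 this is 0.3/0.775 = 0.387, and the noncentrality at n = 30 is 0.387 × √30 = 2.12. One arm's paired t-test is then significant with probability p = 0.536.

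The misleading pattern, at least one Tai Chi arm significant and control not, has probability [1 − (1 − p)²](1 − p), as the arms are independent. Here that is (1 − 0.464²) × 0.464 = 0.364.

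| Common drift (SD), rho 0.7, n = 30 | One arm significant | At least one Tai Chi arm significant, control not |
|---|---|---|
| 0 | 0.050 | 0.093 |
| 0.2 | 0.277 | 0.345 |
| 0.3 | 0.536 | 0.364 |
| 0.5 | 0.927 | 0.072 |

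The pattern becomes rare at large drift because the control arm then turns significant as well.

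**The case against.** Several counter-arguments have force.

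*The between-group tests are valid.* This stands. Allocation is randomised with a concurrent control, so the unadjusted comparisons are not biased and a common time trend cancels in them. A reader might infer that season or re-testing contaminates these comparisons; nothing in the Protocol supports that. What they lose is precision.

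*Change scores may have been meant.* This stands in part. The Introduction speaks of detecting changes in the indicators, and section 3.8.2 does not say what enters the ANOVA, so it goes too far to state that the plan ignores the baseline. But ANCOVA has the smaller variance on either reading, and leaving the choice open lets it be made after the data are seen.

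*The Protocol never says the paired tests decide effectiveness.* True. A reader might infer that it plans to claim a Tai Chi effect from them; the text does not say so. The fault is that their role is left unstated while they share the significance level of the randomised comparisons.

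*Power is already adequate.* At f = 0.40 it is: 0.818 at N = 66 and 0.926 at N = 90 without adjustment. However, section 3.3 takes f = 0.40 as the largest conventional value because no comparable study was found, so it is not an estimate. The gain from adjustment matters most if the true effect is smaller.

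*Adjustment can be left to a statistical analysis plan.* Often it can, but this Protocol already fixes the tests by name, so the point concerns what is written.

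**Conclusion.** The point holds as one of efficiency and clarity. It should be fixed, but it does not invalidate the trial's randomised comparisons. The plan specifies unadjusted between-group tests, leaves the analysed variable open, and does not mark the within-group tests as descriptive.

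The size of the precision gain depends on rho, which the Protocol does not give. For rho between 0.5 and 0.7, ANCOVA cuts the variance of a post-only comparison by 25% to 49%. Against change scores, the variance ratio is 0.75/1.00 = 0.75 at rho 0.5 and 0.51/0.60 = 0.85 at rho 0.7.

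The 54% for one arm's paired test should not be read as the rate of false effectiveness claims. The rate of the misleading pattern is 36% at a drift of 0.3 SD, and between 7% and 36% over the drifts shown. It would do harm only if that pattern were taken as evidence of effect.

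**What to change.** In section 3.8.2, make the between-group analysis of each outcome an ANCOVA of the Visit 3 value on group, with the Visit 2 value as covariate. Report the adjusted contrasts with 95% CIs: each Tai Chi group minus control for the first objective, and one Tai Chi group minus the other for the second. State that these contrasts are the only basis for effectiveness statements. Label the within-group pre/post results descriptive.

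University as a further covariate, a log scale for triglycerides, and dropping the Shapiro-Wilk switch are optional choices that this point does not depend on.

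The cost is protocol wording. Both measurements are already scheduled in section 3.6, no extra participants are needed, and the named software, SPSS 26, fits the model.

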### **3.9 Quality control**

1) Quality control of the informed consent of volunteers: Before signing the informed consent form, extensive education and communication should be carried out by the volunteer participants, so that the volunteers fully understand the content of the informed consent form.

2) Volunteer recruitment quality monitoring: strictly screen, all volunteers according to the inclusion and exclusion criteria.

3) Quality monitoring of random control and blind method: The project manager randomly grouped qualified subjects according to the number of the screener according to the random grouping sequence, properly kept the blind bottom, and unbind after the data analysis is over.

4) Quality control of the intervention process: The project manager supervises the coaching and training process of the coach, and the coach should supervise and guide the training process of the volunteers of the intervention group.

5) Quality monitoring of statistical analysis: The measurement data must be clearly filled in the research report form. Those whose results are zero and those that cannot be detected in the test should be indicated by corresponding symbols and cannot be vacated in order to distinguish them from missing values. If there is a missing value, look up

the original data, and fill it in for missing; if there is no record in the original data, notify the subject to recheck immediately; if the missing value affects the resulting judgment, the case is eliminated.

6) Data management quality control: The list of documents that the project manager must keep is checked one by one. If there are any missing items, the relevant personnel shall be required to fill in them.

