#### **3.1.1 Randomization and allocation concealment**

The eligible participants will be randomly allocated in a 1:1:1 ratio to either the Bafa Wubu Tai Chi group, tradition He-styles Tai Chi group and control group. The random allocation sequence will be generated using web programming at <http://www.randomizer.org> by the project manager. The eligible participants will be informed of their allocation result by the project manager via telephone after their baseline information has been assessed.

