#### **3.2.3 Exit criteria**

- 1) Those who can't insist on training;
- 2) Those who do not practice according to the training requirements;
- 3) Sudden illness or injury occurred during the test and cannot continue to participate in the training;

- 4) Those who voluntarily propose to quit the researcher;
- 5) The control group members practice Tai Chi during the experiment;
- 6) Those who have adverse events and are not suitable to continue practicing.

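### Arm-specific exits and deletion of cases with missing values are likely to leave non-adherent Tai Chi men and Tai Chi-practising controls out of the randomised comparison

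*Protocol*

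**What the plan says.** Participants are "randomly allocated in a 1:1:1 ratio" (Protocol 3.1.1). Section 3.2.3 then lists six exit criteria, all applied after randomisation. Four matter most here:

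- Criterion 1: "Those who can't insist on training".
- Criterion 2: "Those who do not practice according to the training requirements".
- Criterion 5: "The control group members practice Tai Chi during the experiment".
- Criterion 6: "Those who have adverse events and are not suitable to continue practicing".

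Controls have no exercise programme (3.4.3), so criteria 1 and 2 act in effect only in the Tai Chi arms. Criterion 5 acts only in the control arm.

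Section 3.9, item 5, deals with missing values in three steps. The source record is searched. Next, "if there is no record in the original data, notify the subject to recheck immediately". Finally, "if the missing value affects the resulting judgment, the case is eliminated".

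On follow-up, section 3.6 says of Visit 3: "All participants will be participated in the examination as same as the assessment of visit 2". It does not say whether a man who has exited still counts as a participant. Section 3.8.2 compares the three groups without naming who is analysed. Section 3.3 allows 20% for dropout in each group, not divided by cause.

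**The concern.** Randomisation makes the three arms comparable at the start. Removing men afterwards by a rule tied to behaviour, and by a different rule in each arm, undoes that. The Tai Chi men who remain are those who could and did train. The controls who remain are those who did not take up Tai Chi, although all recruits are said to be interested in it (3.2). If adherence goes with a better outcome for any reason, a difference between Tai Chi and control can appear, or be enlarged, without being caused by Tai Chi.

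The elimination clause adds to this. On its milder reading it is complete-case deletion: a man whose outcome cannot be judged is dropped. On its literal reading, deletion depends on what the missing value does to the result. No criterion separates the two.

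The rules bear on every outcome. A man who is not measured at Visit 3 cannot be recovered at the analysis stage.

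**Working it through.** **The plan's own figure.** One-way omnibus F test, f = 0.40, alpha 0.05, three groups, N = 66: λ = N × f² = 66 × 0.16 = 10.56, critical F = 3.1428, power = 0.818. This matches section 3.3.

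**The effect the plan is sized for.** If both Tai Chi arms share one mean and control lies d SD away, the variance of the three means is 2d²/9. So f = d√2/3 and d = 0.40 × 3/√2 = 0.85 SD.

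**Shift in an arm mean from removing men.** With a fraction p removed, the mean of those kept differs from the whole-arm mean by p × (mean of kept − mean of removed). Take p = 0.20 from the dropout allowance; that all of it is selective loss is an assumption, and so are the gaps.

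- Gap 0.5 SD: 0.20 × 0.5 = 0.10 SD, and 0.10/0.85 = 12% of the planned effect.
- Gap 1.0 SD: 0.20 × 1.0 = 0.20 SD, and 0.20/0.85 = 24%.

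With no offsetting loss in control, this shift passes straight into the Tai Chi-control difference.

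**Simulation with no true effect.** Each arm has 30 men, and each Tai Chi arm loses its 20% least adherent (24 kept). Adherence has correlation r with a good outcome.

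| Control exits | r | Spurious Tai Chi-control difference | Omnibus type I error |
|---|---|---|---|
| none | 0 | 0.00 SD | 5.0% |
| none | 0.1 | 0.03 SD | 5.2% |
| none | 0.3 | 0.10 SD | 6.6% |
| none | 0.5 | 0.17 SD | 9.9% |
| none | −0.3 | −0.10 SD | 6.7% |
| 10%, those most inclined to do well | 0.3 | 0.16 SD | 8.7% |
| 20%, same mechanism as Tai Chi arms | 0.3 | about 0 | 5.3% |

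The two calculations connect. Under normality, removing the lowest 20% creates a gap of about 1.75r SD between kept and removed. A 0.5 SD gap therefore needs r of about 0.5/1.75 = 0.29, and a 1.0 SD gap needs about 1.0/1.75 = 0.57, which lies beyond the largest r simulated.

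**If Tai Chi works.** Suppose non-adherers gain nothing and make up a share p of each Tai Chi arm. The adherent-only effect then exceeds the as-randomised effect by 1/(1 − p) − 1: 5% at p = 0.05, 11% at 0.10, 25% at 0.20 and 43% at 0.30.

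**The case against.** The strongest reply is that the protocol never calls its analysis per-protocol. Section 3.2.3 lists reasons for leaving; it does not say that data are discarded or that Visit 3 is skipped. Section 3.6 says all participants are examined. The choice of analysis population is commonly left to a statistical analysis plan, which is not at hand. This stands as far as it goes: that exited men drop out of the comparison is an inference from exit combined with case deletion. But the exit rules and the elimination clause are stated here, and nothing in the document offsets them.

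A reader might infer that cases are deleted according to whether they help the result. The text does not establish that. A value still missing after look-up and recheck is unknown, and the wording may mean only that the outcome cannot be judged. That milder reading is still deletion of randomised men.

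A reader might also infer that the project manager makes these deletions unblinded. That role generates the sequence, holds the code and reviews the forms (3.1.1, 3.1.2, 3.8.1), but no section says who decides an elimination.

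The sizes are open to challenge too. The 20% allowance applies to every group and covers all causes. Illness, injury, voluntary withdrawal and adverse events (criteria 3, 4 and 6) include causes that can also arise in controls. All of this stands, and the figures above are illustrations only.

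**Conclusion.** The point holds in this form. The protocol fixes exits that differ by arm and an undefined deletion rule, and leaves it open whether exited men are measured and analysed as randomised. Followed as written, the comparison is likely to omit non-adherent Tai Chi men and Tai Chi-practising controls, and this would probably favour Tai Chi over control.

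A firmer statement, that the result is biased towards Tai Chi, is tempting but unsupported. With no true effect and no link between adherence and outcome the bias is zero; with a negative link it reverses; with equal losses by the same mechanism in control it vanishes. For Bafa Wubu against He-style, one of the trial's two stated comparisons, the direction cannot be determined.

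Under the stated assumptions (20% of a Tai Chi arm removed, a gap of 0.5 to 1.0 SD, no offsetting control loss) the shift is 0.10 to 0.20 SD against a planned 0.85 SD. That would not by itself produce the planned effect. It could inflate a smaller one or raise the false-positive rate, and the collected data could not show by how much. It should be corrected before follow-up, because unmeasured outcomes cannot be regained.

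**What to change.** Leave the exit criteria unchanged and alter only the wording on follow-up and analysis.

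1. In 3.6, state that Visit 3 is for everyone randomised, whatever their adherence or reason for exit, unless consent to follow-up is withdrawn.
2. In 3.9, item 5, keep the look-up and recheck steps and replace the elimination clause with, for example: *All randomised participants are analysed in their assigned group. Values still missing after look-up and recheck are handled by multiple imputation using arm and baseline values.* Another method would do, provided that one is named in advance.
3. Report the adherent-only set as a labelled sensitivity analysis.

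The cost is some extra attendance at an already planned visit and some analysis work. The estimated effect may be smaller. With all 90 men measured and analysed, power is 0.926 if f = 0.40 holds for everyone randomised. It is 0.766 if 20% gain nothing (f = 0.40 × 0.80 = 0.32). Analysing only 24 per arm at f = 0.40 gives 0.853, but for the adherent-only effect.

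Imputation from arm and baseline cannot correct loss driven by motivation that nobody recorded. Item 1 is therefore the main remedy; item 2 deals with what remains missing.
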